### Additional consent provisions for collection and use of participant data and biological specimens {26b}

Not applicable. There are no plans for additional studies using the data collected in this trial.

### Intervention

#### Explanation for the choice of comparators {6b}

In spite of the effectiveness of cognitive behavioral therapy provided online for depression, only a few trials have studied the applicability of ICBT for the elderly.

#### Intervention description {11a}

Eligible participants will be randomly assigned at a ratio of 1:1 either to a modular cognitive behavioral therapy group with minimal therapist support or a waiting list control group. Participants in the intervention group will receive access for 8 weeks to a tailored modular ICBT. Participants in the waiting list control group will be instructed to wait for 8 weeks before being able to access the intervention. This intervention was originally developed in Sweden and then translated and adapted for the Lithuanian population. A waiting list control group was chosen as a comparator because no other standardized Internet-based intervention for treatment of depression is available in Lithuanian language at this point in time.

All participants will receive the same first (introduction/rationale) and the last (relapse prevention) modules. The remaining modules will be tailored according to the participant’s condition and preferences. Tailoring will be done by selecting any 6 of the following 10 modules: behavioral activation (parts 1 and 2), acceptance, sleep disturbances, worry and anxiety, loneliness, pain, applied relaxation, the nature of emotions, and a life-review module. The intervention is constructed so that most modules begin with some psychoeducation, followed by exercises for participants to practice with and questions about the material presented in the module. Completed exercises and answered questions are then saved and can be assessed by the therapist. The therapists will assess the assignments, provide feedback, and prescribe modules weekly.

A group of three clinical psychologists and two graduate students of clinical psychology will be involved as therapists in this study. Supervision will be provided regularly by a clinical psychologist with experience in CBT and clinical work with patients suffering from anxiety and depression as well as Internet-delivered treatments.

#### Criteria for discontinuing or modifying allocated interventions {11b}

Participants will be instructed to contact the research team personnel if their condition deteriorates. Such a participant will be contacted within 24 h, and a thorough clinical interview will be administered via telephone by an experienced clinical psychologist. Based on the outcome of the interview, the participant might then be referred to a hospital or other appropriate services.

#### Strategies to improve adherence to interventions {11c}

Adherence to the intervention will be monitored through the treatment platform. The platform automatically records participant engagement with the intervention. Recorded activity includes login times, module completion, exercise completion, and number of messages sent to the therapist.

#### Relevant concomitant care permitted or prohibited during the trial {11d}

Ongoing psychopharmacological medications with stable dosage are allowed. Participation in other psychological interventions is prohibited but will not result in withdrawal from the study if started after the intervention. After termination, all participants will be asked about receiving any other intervention during the trial and this information will be reported.

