### Eligibility criteria {10}

Inclusion criteria: Participants eligible for the trial must comply with all of the following at randomization: (1) 60+ years, (2) depressive symptoms, (3) access to a computer/tablet/smartphone and to the Internet, and (4) good knowledge of the Lithuanian language (reading, speaking, and writing without an interpreter). Exclusion criteria: (1) problematic alcohol use, (2) presently in any other psychological treatment, (3) severe depression, (4) suicidal ideation, and (5) significant change in psychiatric medication (during last 6 weeks).

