### Plans to promote participant retention and complete follow-up {18b}

All participants will be informed in the informed consent about follow-up assessments. If participants discontinue or deviate from intervention protocols, they will be contacted and study team members will first try to address any concerns participants might have that are altering their adherence to the intervention protocols. In case these concerns cannot be resolved, participants will then be asked to fill in follow-up self-assessment questionnaires online.

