### Methods in analysis to handle protocol non-adherence and any statistical methods to handle missing data {20c}

Initially, intention-to-treat (ITT) analysis will be performed on all primary outcomes in case of drop-out from the study. Secondary per protocol analyses (PPA) will be performed for those participants who adhered to treatment protocol. In ITT analysis last value carried forward will be used to fill in missing data. In PPA analysis missing cases will be removed on a case-by-case basis and only completed data will be analyzed.

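### The rule on other psychological treatment implies withdrawal from the study for a start before the post-treatment assessment, so a primary outcome score could be lost and replaced by baseline

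*Protocol article*

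**What the plan says.** All references are to the protocol article.

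- **Concomitant care {11d}:** "Participation in other psychological interventions is prohibited but will not result in withdrawal from the study if started after the intervention". The next sentence adds: "After termination, all participants will be asked about receiving any other intervention during the trial and this information will be reported". What happens when other treatment starts earlier is not written.
- **Eligibility {10}:** a person is excluded at entry if "2) presently in any other psychological treatment" applies, so any such treatment during the 8 weeks is a new start after randomisation.
- **Intervention description {11a}:** "Participants in the waiting list control group will be instructed to wait for 8 weeks before being able to access the intervention".
- **Discontinuing or modifying interventions {11b}:** a participant who reports deterioration is interviewed, and "Based on the outcome of the interview, the participant might then be referred to a hospital or other appropriate services". Section {30} also directs deteriorating participants to local services, under post-trial care.
- **Retention {18b}:** those who discontinue or deviate are contacted. If their concerns cannot be resolved, "participants will then be asked to fill in follow-up self-assessment questionnaires online".
- **Non-adherence and missing data {20c}:** "Initially, intention-to-treat (ITT) analysis will be performed on all primary outcomes in case of drop-out from the study". Missing values in that analysis are filled by carrying the last value forward. The per-protocol analysis uses completed data only.
- **Table 1 {13}:** up to the end of the randomised comparison, PHQ-9 and GDS are collected at online screening/baseline and at t9, with nothing between.

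**The concern.** The condition in {11d} has a function only if an earlier start is treated differently, and the consequence it names is withdrawal from the study, not from the intervention. A coordinator could fairly read it as an instruction to stop collecting outcomes from anyone who starts counselling in weeks 1 to 8.

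The arms are not placed alike. Whether the phrase about starting after the intervention means after it begins or after it ends, a control has not had the intervention before t9. The exemption therefore cannot apply to controls at any point before the main between-group comparison. Controls are also the group asked to wait untreated, so they may have more reason to look elsewhere.

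The event may also be related to outcome. Under {11b} the study team may itself refer a deteriorating participant to other services, and such a referral could lead to the treatment that {11d} prohibits. At stake are t9 scores that could have been collected, lost for a reason that may depend on both arm and outcome. They cannot be recovered afterwards.

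**Working it through.** **1. The plan's own figure on losses.** Section {14} inflates 70 for 10% dropout: 70 / (1 - 0.10) = 77.8, rounded up to 78, or 39 per arm. This reproduces. The allowance per arm is 0.10 x 39 = 3.9, about 4 people for all reasons together. Neither the rule in {11d} nor this point changes the sample size.

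**2. What carry-forward would carry.** Between randomisation and t9 there is no further PHQ-9 or GDS. For a participant withdrawn in that window the last value is the baseline value.

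**3. Shift in the control mean.** If k of 39 controls have their t9 score replaced by baseline:

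shift = (k/39) x (mean baseline of those withdrawn - mean t9 they would have had)

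Inputs from {14}: control PHQ-9 14.22 at T1 and 8.11 (SD 4.92) at T2; intervention 12.45 at T1 and 6.57 at T2. Planning difference at T2: 8.11 - 6.57 = 1.54.

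Assumptions: k is 2, 4 or 6 (the documents give no rate); those withdrawn have the average baseline of 14.22; no such withdrawals occur in the other arm.

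*(a) Withdrawal unrelated to outcome.* Baseline minus t9 is 14.22 - 8.11 = 6.11.

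- k = 2: 2/39 x 6.11 = +0.31
- k = 4: 4/39 x 6.11 = +0.63
- k = 6: 6/39 x 6.11 = +0.94

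*(b) The k worst controls withdraw.* With normal t9 scores, the worst 2, 4 or 6 of 39 have mean t9 of 18.21, 16.69 or 15.69.

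- k = 2: 2/39 x (14.22 - 18.21) = -0.20
- k = 4: 4/39 x (14.22 - 16.69) = -0.25
- k = 6: 6/39 x (14.22 - 15.69) = -0.23

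A positive shift enlarges the apparent benefit and a negative one shrinks it. At k = 4 the apparent difference would be 1.54 + 0.63 = 2.17 in case (a) and 1.54 - 0.25 = 1.29 in case (b). If the worst-scoring controls also started above the average baseline, the shift in (b) would be less negative or could turn positive.

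**4. Role of imbalance.** If 4 of 39 were withdrawn in each arm for reasons unrelated to outcome, the intervention mean would rise by 4/39 x (12.45 - 6.57) = 4/39 x 5.88 = 0.60. That nearly cancels the 0.63 in controls. The bias therefore needs withdrawals that differ between arms or depend on outcome. The rule makes both possible, and the documents exclude neither.

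**The case against.** The strongest reply is that no withdrawal rule is written. The sentence is silent on starts during the 8 weeks. The sentence after it has all participants asked about other interventions during the trial, which suggests that those who had some remain available. On this view {18b} supplies the working rule: people who deviate are still asked for questionnaires. An article may also leave such detail to the full protocol. Part of this stands, because withdrawal is an inference from contrast. But it is the natural reading of the words that are there, and the reassuring sentences do not override them. They leave staff with two instructions that point in different directions.

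A reader might go further and infer that the rule contradicts the intention-to-treat plan by deleting participants. The documents do not support that. Section {20c} applies intention to treat expressly to drop-outs, the abstract applies it to all participants, and no section removes a withdrawn participant from that set. Outright deletion of the worst 2 to 6 controls would shift the control mean by -0.55 to -1.38, but that describes a completers-only analysis, not the planned primary one.

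A reader might also infer that the rule removes the participants who fare worst. That is plausible given {11b}, but no data in the document show who would seek other care or how often. Section {11b} speaks only of possible referral, does not mention withdrawal, and does not say that those services count as a psychological intervention under {11d}.

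Finally, 1.54 is only a yardstick. The planning arms already differed at baseline by 14.22 - 12.45 = 1.77 points, so 1.54 is not a clean treatment effect.

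**Conclusion.** The point holds in a limited form. Section {11d} implies withdrawal from the study for other psychological treatment started in the 8 randomised weeks, leaves controls without the exemption until after t9, and is not reconciled with {11b}, {18b} or its own next sentence. The consequence is loss of t9 scores and their replacement by baseline, not exclusion from the intention-to-treat analysis.

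For 4 of 39 controls the resulting shift is between about -0.25 and +0.63 PHQ-9 points in the two cases worked. That is about 16% and 41% of the 1.54-point planning difference (0.25/1.54 and 0.63/1.54). The sign cannot be settled in advance, nor checked later once t9 is not collected. The size rests on an assumed number of withdrawals, about equal to the plan's whole dropout allowance for one arm, with none in the other arm. It shows scale and is not a forecast. The change is a cheap improvement, worth making because it prevents missing data that no analysis can restore.

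**What to change.** Add to {11d} that starting another psychological treatment at any time after randomisation does not end outcome collection. The participant is still asked to complete t9 and all follow-ups and is analysed in the assigned arm. The start date is recorded, and the number of starts is reported by arm. Then reconcile {11b}, {11d}, {30}, {18b} and {20c} so that they give one instruction on collecting outcomes.

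This concerns outcome data only. Clinical care, referral and continued access to the platform remain with the study clinicians.

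The cost is a short amendment, with no extra visits or questionnaires and no change in sample size. One small downside is that some participants will have had outside treatment by t9, so the estimate is of a treatment policy that includes it. The counts by arm let readers judge how much that matters.

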#### Provisions for post-trial care {30}

Participants who show signs of deterioration will be directed to their local mental health center for further treatment.

### Outcomes {12}

Difference between intervention and control groups pre- and post-treatment as well as at 3-month and 1- and 2-year follow-ups will be analyzed for both primary and secondary outcomes. Primary outcomes are depression symptoms measured with the Patient Health Questionnaire (PHQ-9) [29] and Geriatric Depression Scale (GDS) [30]. Secondary outcomes include anxiety symptoms and psychological well-being. Anxiety symptoms will be measured with the Generalized Anxiety Disorder Scale (GAD-7) [31] and levels of psychological well-being will be measured with the World Health Organization Well-being Index (WHO-5) [32]. Difference in means post-treatment will be compared between groups for both primary and secondary outcomes. Within group trial effects will be calculated using difference in means from baseline to post-treatment for all primary and secondary outcomes. Additionally long-term effectiveness of the intervention will be measured comparing outcome differences from post-treatment to 3-month and 1- and 2-year follow-ups.

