## Objectives {7}

The aim of this study is to test the effectiveness of an Internet-based cognitive behavioral therapy with minimal therapist support for depressed older adults. Our hypothesis is that the treatment group will have significantly larger reductions in symptoms of depression when compared to the waiting list control group post-treatment and will retain these effects at the 3-month follow-up. We will further seek to evaluate retention at 12- and 24-month follow-ups.

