## Trial design {8}

This study is a parallel group, two-arm, exploratory trial with a 1:1 allocation ratio and no stratification.

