## Statistical methods

### Statistical methods for primary and secondary outcomes {20a}

Effect sizes for pre- to post-treatment and between-group comparisons for the main and secondary outcomes will be calculated to evaluate the effectiveness of the intervention. Additionally, regression analysis will be performed to test if treatment expectations prior to the beginning of the treatment predict primary and secondary outcomes.

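### The between-group comparison is stated on post-treatment means with no use of the baseline score, which costs precision and leaves the result exposed to chance baseline imbalance

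*Protocol article*

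**What the plan says.** Outcomes {12} gives the between-group comparison in one sentence: "Difference in means post-treatment will be compared between groups for both primary and secondary outcomes". Baseline enters only in the next sentence, arm by arm: "Within group trial effects will be calculated using difference in means from baseline to post-treatment for all primary and secondary outcomes".

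Statistical methods {20a} says "Effect sizes for pre- to post-treatment and between-group comparisons for the main and secondary outcomes will be calculated to evaluate the effectiveness of the intervention". It names no outcome model. The only regression in that section concerns treatment expectancy: "regression analysis will be performed to test if treatment expectations prior to the beginning of the treatment predict primary and secondary outcomes".

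Objectives {7} words the hypothesis in terms of change: "the treatment group will have significantly larger reductions in symptoms of depression when compared to the waiting list control group post-treatment". Sample size {14} describes a power calculation that includes the pre- and post-treatment measurement points. Trial design {8} describes a "two-arm, exploratory trial with a 1:1 allocation ratio and no stratification". Table 1 and section {18a} show that PHQ-9, GDS, GAD-7 and WHO-5 are all completed before randomisation.

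**The concern.** The hypothesis and the power calculation are framed around pre and post scores, but the stated between-group comparison uses only the second of them. There are two consequences.

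- **Precision.** Variation in the post-treatment score that the baseline score predicts stays in the error term.
- **Imbalance.** With unstratified allocation and about 39 per arm, a chance baseline gap of a point or two on PHQ-9 is possible, and a comparison of post-treatment means carries part of it into the estimated effect.

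The within-group effect sizes do use baseline, but they do not fill the gap. Each describes change in one arm, so it does not separate the effect of treatment from anything else that moves scores over eight weeks.

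**Working it through.** **Inputs.** From Sample size {14}, PHQ-9 mean (SD) in the planning study:
- intervention: 12.45 (4.38) before, 6.57 (4.34) after
- control: 14.22 (4.19) before, 8.11 (4.92) after

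Also from {14}: alpha 0.05, taken here as two-sided because sidedness is not stated; 70 participants needed, 78 randomised (39 per arm). The pre-post correlation r is not given, so it is an assumption, ranged over 0.3 to 0.7.

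**The plan's own figures.** 70/0.9 = 77.8, so 78 reproduces. The 70 does not reproduce from these means as a comparison of post-treatment means (143 per arm, step 5) or as a comparison of change. That is a separate matter, and baseline adjustment does not resolve it.

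**1. Pooled SDs.**
- Baseline: √((4.38² + 4.19²)/2) = 4.29
- Post-treatment: √((4.34² + 4.92²)/2) = 4.64

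**2. What the planning data show on each scale.**
- Baseline gap: 14.22 − 12.45 = 1.77, control higher
- Post-treatment gap: 8.11 − 6.57 = 1.54, favouring intervention
- Change: 12.45 − 6.57 = 5.88 (intervention) and 14.22 − 8.11 = 6.11 (control), a difference of 0.23 favouring control

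Post-treatment means and reductions thus point in opposite directions in the protocol's own planning figures.

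**3. Baseline-adjusted planning difference** = 1.54 − r × (4.64/4.29) × 1.77.
- r = 0.4: 0.77
- r = 0.5: 0.58
- r = 0.6: 0.39

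**4. Chance imbalance in this trial.** SE of the baseline difference = 4.29 × √(2/n).
- n = 39: 0.97; P(gap of at least 1.77 in either direction) is about 7%
- n = 35: 1.02; the probability is about 8%

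With 35 per arm, a gap of 1.77 and no treatment effect, the expected post-treatment difference is r × (4.64/4.29) × 1.77, or about 0.6, 1.0 or 1.3 points at r = 0.3, 0.5 or 0.7. The conditional type I error is then about 7, 10 or 15% instead of 5%.

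**5. Precision.** ANCOVA residual SD = 4.64 × √(1 − r²), so residual variance falls by r²: 16, 25 or 36% at r = 0.4, 0.5 or 0.6.

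For a true difference of 1.54, n per arm for 80% power = 2(1.96 + 0.84)² × SD²/1.54². Power is from the t test.

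| Analysis | Residual SD | Power, 35 per arm | n per arm for 80% |
|---|---|---|---|
| Post-treatment means | 4.64 | 28% | 143 |
| ANCOVA, r = 0.3 | 4.43 | 30% | 130 |
| ANCOVA, r = 0.5 | 4.02 | 35% | 107 |
| ANCOVA, r = 0.7 | 3.31 | 48% | 73 |

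**6. Within-group effects in baseline SDs.**
- Intervention: 5.88/4.38 = 1.34
- Control: 6.11/4.19 = 1.46

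**The case against.** The strongest reply is that this is silence, not a choice. The Outcomes section names outcomes and contrasts, not models; an ANCOVA also compares post-treatment means, after adjustment; and nothing says the means will be unadjusted. The opening sentence of Outcomes {12}, which refers to differences between groups pre- and post-treatment, could be read as including change. A separate analysis plan might settle it, and the trial calls itself exploratory. This lowers the weight of the point. It does not remove it: the article goes on to specify the contrast, defines no between-group comparison of change and no adjusted comparison, and still hypothesises a significant difference.

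Several stronger readings are tempting and not supported.

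- **That the comparison is biased.** Under randomisation it is unbiased on average and keeps its nominal error rate. The problem is conditional on the imbalance observed, and a gap as large as 1.77 is uncommon.
- **That the planning difference is wholly baseline imbalance.** Between 0.39 and 0.77 points remain after adjustment at r = 0.4 to 0.6. It vanishes only if the full baseline gap is subtracted.
- **That adjustment lifts power from 80% to about 90%.** That holds at r = 0.5 for a standardised difference of 0.68 (3.15 points), a value solved backwards from 35 per arm and found nowhere in the protocol.
- **That the planning control group shows natural recovery.** The protocol does not describe that control condition or how that study allocated participants.
- **That a within-group effect alone would establish effectiveness.** The protocol lists these effects beside the between-group ones, but its hypothesis is between-group.

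**Conclusion.** The point holds as a recommended improvement, not as an error that invalidates the trial. As written, the between-group test makes no use of a baseline score that every participant supplies, and it does not match a hypothesis about reductions.

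The gain in precision depends on a correlation the protocol does not give, and restricted eligibility (depressive symptoms required, severe depression excluded) could put it towards the lower end of the range. On the protocol's own 1.54-point difference the gain in power is modest to moderate, and adjustment does not by itself deliver the stated 80%. The planning data illustrate the sensitivity to imbalance well: the post-treatment difference there largely reflects the baseline gap. They also show why within-group effects should carry no inferential weight, since the control arm's pre-post effect was at least as large as the intervention arm's.

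**What to change.** In {12} and {20a}, define the effectiveness analysis as the between-group difference in PHQ-9 at t9 from an ANCOVA, or an equivalent mixed model, with arm and baseline PHQ-9 as terms. Report it with a 95% CI and a two-sided test at 0.05. Analyse GDS, GAD-7 and WHO-5 in the same way, each with its own baseline. Derive the between-group effect size from the adjusted difference, and state that within-group pre-post effects are descriptive only.

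The cost is wording. No new data are needed, because every covariate is already in the schedule. The change should be fixed while the data analysts are still blinded to group, and go through the ethics committee and trial register as section {25} requires for amendments.
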